**Intervention or treatment**

**Antimalarial Therapy-** All Pf patients enrolled into the study will be given AL while all Pv patients will be assigned to a drug group (AL or CQ) using a random number table. All drugs administered in the facility will be under supervision by the staff. Patients will be observed for 60 minutes after treatment for adverse reactions or vomiting. Those patients vomiting their medication within the first 30 minutes will receive a repeat full dose, those vomiting from 30-60 minutes will receive half dose. This is standard practice for anti-malarial treatment.

**Rescue Treatment**

Patients failing in any arm will be treated with quinine 10mg/kg/dose every 8 hours for 7 days as per National Guidelines [24]. This treatment will be administered orally unless the patient has persistent vomiting, in which case he/she will receive IM/IV therapy until able to tolerate oral therapy.

**Concomitant Treatment** Using standard clinic procedures, clinic personnel will administer supportive treatment to patients as necessary:

- **Antipyretics** will be given for temperatures > 39oC as per national policy. All patients enrolled in the study will be given two additional doses of paracetamol for use at home. Patients/parents/guardians should be instructed in the use and application of tepid sponging and fanning as per national policy.
- **Ferrous Sulfate/ Folate** will be given to all children with hemoglobin <10 mg/dl as per Integrated Management of Childhood Illness (IMCI) Guidelines
- **Anti-helminthics** will be given to children with hemoglobin <10 mg/dl over one year of age as per IMCI Guidelines

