**Exclusion criteria for enrollment:**

1. General danger signs or symptoms of severe malaria (see Annex III)

2. Signs or symptoms of severe malnutrition, defined as weight-for-age ≤ 3 standard deviations below the mean (NCHS/WHO normalized reference values; see Annex IV)

3. Slide confirmed infection with any other *Plasmodium spp.* besides falciparum/vivax or mixed plasmodium infection

4. Severe anemia, defined as Hg < 5 g/dl

5. Known hypersensitivity to any of the drugs being evaluated

6. Presence of febrile conditions caused by diseases other than malaria

7. Serious or chronic medical condition (cardiac, renal, hepatic diseases, sickle cell disease, HIV/AIDS)

8. Pregnant or breastfeeding women.

9. Children weighing less than 5 kilograms.

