**Enrollment Procedures**

If a patient meets the initial screening criteria and permission to participate in the study is obtained, the patient will go through the enrolling process.

1. Patient will be evaluated by clinical staff for signs of febrile illness other than malaria, (including but not limited to pneumonia, otitis media, tonsillitis, measles, chicken pox, abscesses) and signs of severe disease/ danger signs, as presence of any of these will exclude the patient from participating in the study. Patients found to have any of these conditions will be treated appropriately per National Guidelines, and referred to the referral hospital as necessary. A standardized form listing demographic and clinical information will be completed on each patient.

2. Urine pregnancy test will be conducted on all women aged 13-49. Anyone testing positive will be excluded.

3. Those enrolled will have a second finger prick performed to assess for the following:

● Thin smear will be used to verify parasite species and to conduct a formal parasite count. Two microscopists will independently read each smear (one at the study site and the other at Adama Reference Laboratory); if the 2 readings are >20% discordant, a third expert microscopist at the Oromia Regional Laboratory will examine the slide and make the final decision.

- Hemoglobin measurement (Hemocue™ Hb201+; HemoCue, Angelholm, Sweden) will be carried out and those with hemoglobin <5g/dL will be excluded.
- Filter paper will be obtained for molecular testing and drug levels.

4. Consecutive patients testing positive for Pf will be enrolled and treated with AL if they meet all inclusion criteria. Patients testing positive for Pv will be randomized to either CQ or AL treatment arms. A permuted block randomization technique will be used to ensure equal numbers in the two treatment arms. The study will not be blinded, although microscopists reading blood films will not be aware of which arm a participant is from.

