5. After assignment, on day 0, each patient will receive the morning dose of treatment medication under direct observation and will be monitored for vomiting. The patient or parent will be given the evening dose (for AL only) to administer at home. Each patient will return on days 1 and 2 for subsequent doses. Clinical reassessments will be made on days 1- 3, 7, 14, 21, 28, 35, and 42 (see Annex V for a table of scheduled procedures). Participants will be given 35 Ethiopian Birr for each visit to cover their travel expenses (this is enough to cover round-trip transportation by bus to the clinic for one adult; parent traveling with the enrolled child requiring their own seat (age >6 years) will receive 50 Birr). Patients will be advised to return on *any* day during the follow-up period if symptoms return and not to wait for scheduled visit days. Patients who do not present to the facility for follow-up visits will be followed at home. This is standard for in vivo studies based on the WHO protocol, but is not the standard for routine care. Typically, for patients not enrolled in a study, the parent would be given all the doses of the medicine to administer at home, and no follow-up would be scheduled. The parent would be told to return if the child did not improve.

6. Blood films (thick and thin) for parasite count will be obtained and examined at each visit except day 1 and on any other day if the patient spontaneously returns with fever or worsening symptoms. Hemoglobin status will be measured on days 0, 7, 14, 21, 28, 35, and 42. A filter paper blood spot will be collected on days 0 and in case of treatment failure. All molecular testing will be conducted in Addis Ababa, Ethiopia, by Ethiopia Health and Nutrition Research Institute (EHNRI). Blood drug level testing capacity does not currently exist in Ethiopia and will be conducted at CDC Atlanta. All samples will have the study ID number and date of collection, but no other personal identifiers. The logbook that links the study ID number to the patient will be kept at the study site locked in a cabinet when not in use during the study enrollment period. After the completion of the study, this logbook will be stored in a locked cabinet in Addis Ababa at the International Center for AIDS Care and Treatment Program’s office.

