**EMERGENCY CARE**

Any patient with treatment failure or recrudescence will receive quinine 10mg/kg/dose every 8 hours for 7 days. This will be given orally unless the patient has persistent vomiting, in which case it will be given IM/IV until the vomiting resolves and then will be switched to oral therapy.

Patients with signs of severe malaria (altered mental status, coma, convulsions, hemoglobin <5g/dl, Respiratory distress, circulatory collapse, or abnormal bleeding), persistent vomiting or severe side effects will be hospitalized and receive parenteral therapy with quinine and relevant supportive treatments, according to National Guidelines.

Any participant who develops urticaria or difficulty breathing following administration of the treatment drug will be treated with diphenhydramine or chlorpheniramine and will be withdrawn from the study. In addition, patient and or their parents, caretakers and family members will be counseled that the patient should not receive additional doses of the antimalarial they were given. These patients will be treated with oral quinine for seven days as per the rescue protocol.

Adult patients and parents with children in the study will be encouraged to return to the clinic for any fever or other signs of illness on any day during the 42 day follow-up period, allowing for early detection and treatment of illness before it becomes severe.

Any hospitalization which occurs during the 42 day follow-up period will be paid for by the study.

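### The hemoglobin trigger for iron/folate and anti-helminthics is printed in mg/dl while every other hemoglobin limit is in g/dl, so read literally no enrolled child could qualify for either treatment

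*Protocol*

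**What the plan says.** Two bullets under Concomitant Treatment, in the protocol's Rescue Treatment section, carry a hemoglobin trigger. The first concerns ferrous sulfate/folate, which, it says, "will be given to all children with hemoglobin <10 mg/dl as per Integrated Management of Childhood Illness (IMCI) Guidelines". The second bullet sets the rule for deworming drugs, which, in its words, "will be given to children with hemoglobin <10 mg/dl over one year of age as per IMCI Guidelines". Both use mg/dl.

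The other hemoglobin limits use g/dl:

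- Exclusion criteria for enrollment, item 4: "Severe anemia, defined as Hg < 5 g/dl".
- Enrollment Procedures, item 3, on the day-0 finger-prick measurement: "those with hemoglobin <5g/dL will be excluded".
- Emergency Care, in its list of who goes to hospital: "Patients with signs of severe malaria (altered mental status, coma, convulsions, hemoglobin <5g/dl, Respiratory distress, circulatory collapse, or abnormal bleeding), persistent vomiting or" (the list then closes with one more category).

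Annex III lists severe anemia among the manifestations of severe malaria but gives no value. On timing, Enrollment Procedures, item 6, states: "Hemoglobin status will be measured on days 0, 7, 14, 21, 28, 35, and 42". The supportive-treatment trigger is not restated or corrected anywhere else.

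**The concern.** A threshold that decides whether a child receives a treatment must be one that a patient in the study can meet. This one is expressed in a unit 1,000 times smaller than the unit used for every other hemoglobin limit in the same document, and the value was not rescaled to match. The bullets are operative instructions to clinic staff, not background text, so a unit error here is an error in a decision rule.

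What is at stake is the two named supportive treatments. The protocol commits to giving them to children with low hemoglobin, but the literal wording gives them to nobody. To act on the commitment, staff must override the printed figure. A site form or operating procedure copied from the protocol would carry the same unit.

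**Working it through.** The printed trigger is stated, not derived, so there is no calculation of the plan's to reproduce. The check is a unit conversion followed by a comparison of the limits.

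**Inputs**

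- Supportive-treatment trigger: hemoglobin below 10 mg/dl (Concomitant Treatment, both bullets).
- Exclusion limit: hemoglobin below 5 g/dl (Exclusion criteria, item 4; Enrollment Procedures, item 3).
- Severe-malaria sign after enrollment: hemoglobin below 5 g/dl (Emergency Care).

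**Step 1: common unit.** 1 g = 1,000 mg, so the trigger is 10 / 1,000 = 0.01 g/dl. In the other direction, the exclusion limit is 5 × 1,000 = 5,000 mg/dl.

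**Step 2: ratio.** 5 / 0.01 = 500, or equivalently 5,000 / 10 = 500. The literal trigger is 500 times below the exclusion limit.

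**Step 3: day 0.** Every hemoglobin value below 0.01 g/dl is also below 5 g/dl. Patients below 5 g/dl are excluded, so every correctly enrolled child has at least 5 g/dl. No such child meets the trigger.

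**Step 4: follow-up.** A child whose hemoglobin falls after enrollment crosses 5 g/dl first. At that point Emergency Care provides for hospitalization, parenteral treatment and supportive care, and progression to severe malaria is a listed withdrawal criterion. The trigger would require a further 500-fold fall below that limit. It cannot be reached while the child is still managed under the Concomitant Treatment bullets.

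**Step 5: does any planned result use the trigger?**

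- Sample size: built on an assumed 90% response, 120 subjects per arm and 20% loss to follow-up. Hemoglobin is not an input.
- *P. falciparum* outcomes: defined by parasitemia, temperature or fever history, and danger signs or severe malaria. Hemoglobin could enter only through severe malaria, where Emergency Care uses 5 g/dl, not the supportive-treatment trigger.
- *P. vivax* outcomes: defined by parasitemia, temperature, and clinical deterioration requiring hospitalization. The trigger plays no part.
- Data analysis plan: anemia appears only as a frequency by treatment arm, beside side effects, severe malaria and hospitalizations. No hemoglobin-recovery estimate is listed.

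The trigger therefore does not enter any sample-size figure, outcome definition or confidence interval in the protocol.

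**The case against.** The strongest reply is that this is an obvious slip. A hemoglobin of 0.01 g/dl does not occur in a living patient, so nobody would apply the rule literally. The text introducing the bullets relies on the clinics' usual procedures, and both bullets defer to the IMCI guidelines. The two bullets are adjacent and nearly identical in wording, so the repetition fits one slip copied once. All of this stands. It makes harm less likely and limits the weight of the point. It does not make the text right: the guideline's value is not reproduced in the protocol, and following the guideline means setting aside the protocol's own number.

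Three stronger readings are tempting, and the documents do not support them.

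- *A reader might infer that anemic children are left without any care.* Only iron/folate and anti-helminthics are affected. Emergency Care separately covers hemoglobin below 5 g/dl.
- *A reader might infer that sites will interpret the unit differently and so treat children inconsistently.* The only other hemoglobin unit in the protocol is g/dl. Nothing points to a second plausible reading that would divide the sites.
- *A reader might infer that uneven iron use would bias the efficacy comparison.* Hematologic parameters do appear in the general objective, and hemoglobin is measured on seven scheduled days. But the specific objectives and the outcome definitions do not rest on hemoglobin recovery, and the analysis list has anemia only as a frequency. The two *P. vivax* arms are randomized, and nothing suggests that the slip would act differently by arm. The Limitations paragraph also says that the study is not powered to estimate differences between arms.

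**Conclusion.** The point holds as a unit inconsistency in an operative treatment rule. The two supportive-treatment triggers are printed in mg/dl; the three other numerical hemoglobin limits are in g/dl. Read literally, the trigger is 0.01 g/dl, 500 times below the 5 g/dl exclusion limit, and 0% of correctly enrolled children could qualify for iron/folate or anti-helminthics.

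The 500-fold factor is exact and rests only on the printed values. That the cause is a unit slip is a judgment, though a likely one. The cited IMCI guideline is not at hand, so this review does not say what the threshold should be. The consequence is confined to the clarity of a care instruction and leaves the planned efficacy results as they are. Correction is warranted because the rule concerns patient care, is wrong as written and costs almost nothing to repair.

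**What to change.** Reconcile the unit in both Concomitant Treatment bullets with the g/dl limits in the exclusion criteria, the enrollment procedures and Emergency Care, and check the value against the IMCI guideline that the bullets cite. The clinical investigators should settle the threshold from that source. Carry the reconciled value and unit into the site forms so that they match the protocol.

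The cost is two corrected lines and a check of the forms. No sample-size, outcome or analysis text needs to change, and no new data collection is needed to resolve the contradiction.

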### Population

**Description and source of population and catchment area**The population of interest consists of patients aged above 6 months living in malarious areas diagnosed with uncomplicated *P. falciparum* or *P. vivax* malaria consulting at the health facility, who or whose parents or guardians give permission for study inclusion. For logistical reasons, only patients living near the enrolling health care facilities will be included (within 20 km), as we plan to visit the houses of those patients who do not return for scheduled follow-ups.

**Initial screening *inclusion* criteria:**

- Slide-confirmed infection with *P. falciparum*, with parasitemia of 1,000-100,000 asexual forms/ μlor slide confirmed infection with *P. vivax* with > 250 asexual forms/ μl
- Lives within 20 km of the enrolling health facility

**Inclusion criteria for enrollment:**

1. Meet screening inclusion criteria
2. Weight ≥ 5.0 kg
3. Axillary temperature ≥ 37.5º C or history of fever during the previous 24 or 48 hours for *P. falciparum* and *P. vivax* infection, respectively
4. Patient or caregiver agrees to all blood draws and return visits.

**Exclusion criteria for enrollment:**

1. General danger signs or symptoms of severe malaria (see Annex III)

2. Signs or symptoms of severe malnutrition, defined as weight-for-age ≤ 3 standard deviations below the mean (NCHS/WHO normalized reference values; see Annex IV)

3. Slide confirmed infection with any other *Plasmodium spp.* besides falciparum/vivax or mixed plasmodium infection

4. Severe anemia, defined as Hg < 5 g/dl

5. Known hypersensitivity to any of the drugs being evaluated

6. Presence of febrile conditions caused by diseases other than malaria

7. Serious or chronic medical condition (cardiac, renal, hepatic diseases, sickle cell disease, HIV/AIDS)

8. Pregnant or breastfeeding women.

9. Children weighing less than 5 kilograms.

**Justification of exclusion criteria**

Patients with history of danger signs, physical findings of severe illness or life-threatening anemia will be excluded and diverted for immediate management of their conditions. Those with non-malarial febrile illness in addition to malaria or mixed Plasmodium infections will be excluded because this will interfere with our ability to correctly classify the response to therapy. Patients with known sensitivity to drugs must be excluded and treated with an acceptable alternative per national guidelines. Those who plan to leave the study area during the follow-up period or living more than 20 km from the health center will also be excluded so as to minimize loss to follow-up and/or incomplete evaluation and treatment. Because we intend to follow participants at home in the event that they do not present for scheduled follow-up appointments, we need to restrict enrollees to those who live within 20 km of the health facility. Children less than 5 kilograms and pregnant or breastfeeding women will be excluded because there is limited data on drug dosing and safety in those groups.

**Sampling, sample size and statistical power**

i. Sample size determination:

With treatment failure of AL for either Pv or Pf and CQ for Pv in Ethiopia being reported at ≤5%, 10% has been chosen as the estimated therapeutic failure rate of the drugs. Therefore, we assumed an estimated ACPR of 90% for each drug investigated when determining sample size. Allowing for a 20% loss to follow-up at 42 days, a sample size of 120 subjects for each treatment arm will result in a 95% exact binomial confidence interval from 82.4%-95.1%.

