# DATA HANDLING AND ANALYSIS

**Data analysis plan, including statistical methodology and planned tables and figures**

SAS 9.1 (Cary, NC) as well as the WHO drug efficacy tools provided at <http://www.who.int/malaria/toolsformonitoring.html> will be used for data management and analysis. Data will be analyzed using two methods: **per protocol analysis**, where patients who were withdrawn from the study or who were lost to follow-up are excluded, and **survival analysis**, where all enrolled patients are included in the analysis until the last day before drop-out. In addition to voluntary withdrawals or treatment non-compliance, patients will be considered for the analysis as withdrawn if the PCR results are unclassifiable.

The final analysis will include:

- A description of the patients screened, and the distribution of the reasons for exclusion.
- A description of the patients included in the study.
- The proportion of patients lost to follow-up or withdrawn and the distribution of reasons for withdrawal.
- The PCR-adjusted and unadjusted proportion of ETF, LCF, LPF, and ACPR in the Pf arm at day 28 and day 42 with 95% confidence intervals using both methods of analysis.
- Both drug-level and PCR-adjusted and unadjusted proportion of treatment failures in each Pv arm at day 28 and day 42 with 95% confidence intervals using both methods of analysis
- Frequency of side effects, severe malaria, anemia, and hospitalizations by treatment arm

**Data collection**: Data will be collected and recorded at the health facility by one of the trained staff members. All data entry forms will be checked for completeness. Laboratorians may complete brief reports on laboratory findings to share with clinicians who will transfer these results to the case report form of the appropriate patient, the laboratory results will be entered into an Excel database.

**Information management and analysis software:** Microsoft Excel (Redmond, Washington) will be used for double entry of laboratory data and clinical data. SAS 9.1 (Cary, NC) will be used for data analysis.

**Data entry, editing, handling, storage and disposition**: Some open-ended data including the names of specific drugs or diagnoses will be coded prior to data entry. A list of standard codes for these fields will be developed by hand once collection of data is complete. All forms will then be coded and checked by 2 different team members.

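### The stated precision of 82.4% to 95.1% belongs to 100 evaluable patients per arm, but 120 enrolled with 20% loss leaves 96; the effect is small and one sentence corrects it

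*Protocol*

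**What the plan says.** The protocol section on sampling, sample size and statistical power fixes the inputs and gives one result:

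- Response rate: "we assumed an estimated ACPR of 90% for each drug investigated when determining sample size".
- Attrition: "Allowing for a 20% loss to follow-up at 42 days".
- Enrolment and result: "a sample size of 120 subjects for each treatment arm will result in a 95% exact binomial confidence interval from 82.4%-95.1" (per cent).

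It states neither the number expected to be evaluable nor how 120 was reached.

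The data analysis plan defines the per-protocol analysis as one "where patients who were withdrawn from the study or who were lost to follow-up are excluded". It adds that "patients will be considered for the analysis as withdrawn if the PCR results are unclassifiable". A survival analysis keeps every enrolled patient up to drop-out. The Limitations paragraph says that the study is not powered for differences between arms or between sites.

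**The concern.** The sentence makes a checkable claim: this enrolment, less this loss, gives this interval. A reader who takes 20% off 120 and computes the exact interval at 90% gets different limits.

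This interval is the protocol's only quantitative justification of sample size, and it is claimed for each of the three arms (AL for *P. falciparum*, AL for *P. vivax*, CQ for *P. vivax*). The study disclaims power for comparisons, so within-arm precision is its only numerical design target. That figure should be reproducible from the inputs printed beside it.

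**Working it through.** **Inputs, all from the sample-size paragraph:** response p = 0.90; loss to follow-up d = 0.20; enrolled N = 120 per arm; two-sided 95% exact binomial interval.

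**Formula.** For x responders among n, the Clopper-Pearson limits are

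- lower = the 0.025 quantile of Beta(x, n − x + 1)
- upper = the 0.975 quantile of Beta(x + 1, n − x)

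**Step 1: reproduce the plan's figure.** With x = 90 and n = 100 the limits are 82.38% and 95.10%, which is the stated interval. A search over all whole-number x for n from 60 to 140 finds no other pair that gives both limits to one decimal.

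**Step 2: evaluable number from the plan's own inputs.** N(1 − d) = 120 x 0.80 = 96.

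**Step 3: intervals at the candidate sample sizes.** Since 0.90 x 96 = 86.4 is not a whole number, the table gives the value at exactly 90% and at the two neighbouring counts.

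| n | x | Response | Exact 95% CI | Width (points) |
|---|---|---|---|---|
| 100 | 90 | 90.0% | 82.4%–95.1% | 12.7 |
| 96 | 86.4 | 90.0% | 82.2%–95.2% | 13.0 |
| 96 | 86 | 89.6% | 81.7%–94.9% | 13.2 |
| 96 | 87 | 90.6% | 82.9%–95.6% | 12.7 |
| 120 | 108 | 90.0% | 83.2%–94.7% | 11.5 |

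The stated interval matches neither the 96 left after the stated loss nor the 120 enrolled.

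**Step 4: other interval methods.** Normal, Wilson, Agresti-Coull and Jeffreys intervals at n = 96 and n = 120 do not give both stated limits either. The choice of method does not explain the figure.

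**Step 5: likely origin.** To keep 100 evaluable after 20% loss, enrolment must be 100/(1 − 0.20) = 125. Adding 20% to 100 gives 100 x 1.2 = 120, the protocol's number. Going from 120 to 100 is a loss of 20/120 = 16.7%, not 20%.

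**Step 6: size, like for like at 90%.** Lower limit: 82.38 − 82.18 = 0.20 points lower. Upper limit: 95.19 − 95.10 = 0.09 points higher. Width: 13.00 − 12.72 = 0.28 points wider.

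**Step 7: further exclusions.** The protocol gives no rate for withdrawals or unclassifiable PCR results. As an assumed illustration, 90 evaluable with 81 responders (90%) gives 81.9% to 95.3%, a width of 13.5 points.

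**The case against.** The strongest reply is that the discrepancy is negligible.

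- **Size.** At the assumed 90% the limits move by 0.2 points or less. This stands.
- **A reader might infer a 0.7-point fall in the lower limit,** by comparing 82.4% with the 81.7% for 86/96. That comparison also lowers the response from 90% to 89.6%, and most of the 0.7 comes from that rounding. Rounding up to 87/96 gives a lower limit of 82.9%, above the stated one, and a width no larger than stated. Only the comparison at 90% isolates the effect of 96 against 100.
- **A reader might infer that the study is too small for its purpose.** The documents do not support this. The aim is to estimate efficacy, and no test, margin or threshold is tied to 82.4%. The 10% failure rate was chosen above the reported 5% or less. With about 5% failure, 91/96 gives 88.3% to 98.3%, a width of 10.0 points. The survival analysis also uses lost patients up to drop-out.
- **A reader might take 100 x 1.2 as established.** It is an inference, because the protocol never mentions 100 evaluable patients. The mismatch does not depend on it.
- **A reader might treat 96 as a firm upper bound.** The per-protocol definition does remove more than losses to follow-up, but the 20% may have been meant loosely as an allowance for all attrition. Unclassifiable PCR results can also arise only in patients with recurrent parasitaemia, about 10% on the plan's assumption. So the further reduction is conditional and has no rate in the protocol.

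None of these replies makes the printed interval follow from the printed inputs.

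**Conclusion.** The point holds as a minor arithmetic error. The stated interval is that of 90/100, while the protocol's own enrolment and loss leave 96 evaluable, for which the exact interval at 90% is about 82.2% to 95.2%. The cost in precision is about 0.3 points of width. It changes no decision and casts no doubt on the study's validity.

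This rests on reading the 20% as a proportion of those enrolled, which is the plain sense of the text, and on the per-protocol analysis being the one that the binomial interval describes. Any reduction below 96 depends on exclusion rates that the protocol does not give.

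**What to change.** Restate the last sentence of the sample-size paragraph, keeping the 90% assumption. For example: with 120 enrolled per arm and 20% lost by day 42, 96 are expected to be evaluable; at 90% ACPR the exact 95% confidence interval is about 82.2% to 95.2% (81.7% to 94.9% for 86/96, 82.9% to 95.6% for 87/96).

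Add one clause saying whether the 20% is meant to cover withdrawals and unclassifiable PCR results. If it is not, say that they reduce the per-protocol denominator further, and give an assumed figure such as 90 evaluable (81.9% to 95.3%).

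The cost is one or two sentences, with no change to enrolment or conduct. The alternative is to keep the printed interval and enrol 125 per arm (125 x 0.80 = 100), which is 5 more patients per arm and 15 over three arms. A gain of about 0.3 points in width hardly calls for that, so restating is the proportionate choice.
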